### New Lesions

New intrahepatic and extrahepatic lesions are defined as per mRECIST criteria.

- For extrahepatic progression mRECIST criteria excludes ascites and pleural effusion unless cytologically confirmed but otherwise retains the RECIST v1.1 criteria for measurable disease.

### Summary of Response Assessment

**Table 6: Summary of Response Assessment**

| **mRECIST** | **RECIST v1.1** |
| --- | --- |
| **Primary Target Lesion**  **Typical lesion**: ≥ 20% increase in diameter of viable (arterially enhancing) tumour from nadir with absolute increase of ≥5 mm, excluding intervening areas of necrosis.  **Atypical lesion**: measure as per RECIST v1.1 | **Target lesion**  If equivocal or discordant review findings on mRECIST then a ≥ 20% increase in diameter of target lesion from nadir with absolute increase of ≥5 mm as per RECIST v1.1. will be scored as a local progression event. |
| **New Intrahepatic Lesions**  **Typical lesion**: new lesion ≥1cm  **Atypical lesion**: requires increase in size of nodular lesion by ≥ 1cm on serial imaging.  **Macrovascular invasion**: new arterially enhancing vascular thrombus. |  |
| **Extrahepatic Lesions**  As per RECIST v1.1 with the exception that new or progressing ascites and pleural effusion are excluded unless cytologically confirmed and peri-portal lymph nodes should be ≥20mm short axis. | **Extrahepatic Lesions**  Any lesion that is detected at a given post-baseline timepoint and has no corresponding lesion on baseline imaging and is unequivocally malignant will be considered as evidence of disease progression.  Small or equivocal lesions should be reassessed with interval imaging. |

## Definitions of (non-PD) target lesion responses

- Complete Response (CR)
  - mRECIST: The disappearance of any intratumoural arterial enhancement in the target lesion
  - RECIST v1.1: The disappearance of the target lesion (including all lymph node short axis diameters regressed to normal, i.e., short axis that shrinks to <1 cm)
- Partial Response (PR)
  - mRECIST: At least a 30% decrease in the longest viable tumour diameter of target lesion from baseline
  - RECIST v1.1: At least a 30% decrease in the pertinent diameter of the target lesion, from baseline
- Stable Disease (SD)
  - mRECIST: The disappearance of any intratumoural arterial enhancement in the target lesion
  - RECIST v1.1: The disappearance of the target lesion (including all lymph node short axis diameters regressed to normal, i.e., short axis that shrinks to <1 cm)

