“Atypical” intrahepatic lesions are defined in mRECIST as non-enhancing or rim enhancing lesions. These features can be seen in well differentiated, steatotic or poorly differentiated tumours and have often undergone biopsy confirmation. For these lesions RECIST v1.1 criteria, i.e. overall tumour diameter measurements, should apply. A new atypical intrahepatic lesion is regarded as equivocal until interval growth ≥10mm is demonstrated on subsequent scans.

Whilst mRECIST has advantages for response assessment in the setting of thermal ablation, TACE and some systemic therapies, the distinct mechanism of action of radiation-based therapies introduces further challenges. For radiation-based therapies such as radio-embolisation and SABR, both persistent arterial phase hyperenhancement within the target lesion and geographic arterial phase hyperenhancement without washout in the adjacent parenchyma are common in the first 3-12 months following treatment.(45) In contrast to thermal ablation or TACE, residual enhancement in this period is not predictive of subsequent local progression. (46)

The distinct natural progression of target lesion and adjacent parenchymal changes following SABR has been illustrated by Mendiratta-Lala and colleagues.(46) In the first 3 to 12 months following SABR, the arterial phase hyperenhancement gradually converts to portal venous and delayed phase hyperenhancement, as radiation induced veno-occlusion and fibrosis develops, with overlying capsular retraction. Lack of washout or other features such as diffusion restriction can help differentiate expected post-radiation perfusional changes from infiltrative tumour. Radiation-induced biliary strictures, and their associated distal segmental changes, can develop after SABR for more central tumours. Despite mRECIST response having a lower predictive ability in the early months following SABR, with the majority demonstrating stable disease, subsequent new nodular or increasing volume and intensity of arterial phase hyperenhancement with washout are indicators of progressive disease.

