# DISEASE PROGRESSION

Participants will undergo regular tumour assessment (multiphase contrast-enhanced CT or MRI of the liver) as per **Table 5: Schedule of Assessments** until disease progression, withdrawal, end of trial, or death, whichever occurs first. See **APPENDIX 3: Imaging Guidelines** for recommendations on specific imaging sequences.

- Baseline tumour measurements must be undertaken prior to any protocol treatment commencing. (see **Figure 2: mRECIST assessment of tumour lesions at baseline** for target lesion definition). The initial assessment of response will be determined after all protocol treatment has been completed, irrespective whether all of the planned treatment was delivered.
- The target lesion is to be assessed by mRECIST and RECIST v1.1 criteria (see sections **8.1 Definition of Progression** and **8.2 Definitions of (non-PD) target lesion** responses and **Figure 3: mRECIST assessment of tumour response**) at each applicable follow-up timepoint until progression.

Local progression is defined as at the first timepoint that either mRECIST **or** RECIST v1.1 criteria for progression are met. In addition, for cohort 1 (thermal ablation verses SABR) local progression will include the development of any new lesions within 10mm of the ablation cavity following thermal ablation or within 15mm of the target lesion following SABR.

In the event of a progression event, or if the investigator is in doubt as to whether progression has occurred, the imaging should be submitted for central radiological review and no further therapy undertaken until unequivocal progression has been confirmed. Repeat imaging at the next scheduled assessment, or sooner if clinically indicated, is recommended for equivocal findings. If subsequent repeat imaging confirms unequivocal progression the date of the initial imaging will be used as the date of progression. Please refer to section 14.7.4 for further details.

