## Definition of Progression

### Local progression

Target lesion progression will be assessed by mRECIST and RECIST v1.1. If arterial phase enhancement cannot be used then RECIST v1.1 criteria for progression will apply (see **Table 7: Summary of Response Assessment**).

- For **typical** lesions, local progression is defined by evaluation of the target lesion as measured by mRECIST criteria, i.e. an increase of ≥20% (compared to nadir) in longest diameter of viable arterial enhancing tumour with an absolute increase of ≥5mm, excluding intervening areas of complete necrosis. (43)

The longest viable tumour diameter may or may not be located in the same scan plane in which the baseline longest viable tumour diameter was measured.

- For **atypical** lesions (non-arterially enhancing or rim-enhancing at baseline) or for those lesions with equivocal or discordant central review mRECIST findings, progression according to RECIST v1.1 criteria will also be scored as a local progression event, i.e. an increase of ≥20% (compared to nadir) in longest diameter of the whole target lesion with an absolute increase of ≥5mm. (56)

Equivocal findings or discordant central radiological assessments should be confirmed with interval imaging and additional therapy should not be undertaken until unequivocal progression has been confirmed. Equivocal findings are expected to be more common for the radiation-based therapies (TARE and SABR).

Additionally, for Cohort 1, local progression will include any recurrence within 10mm of the ablation zone for MWA/RFA or within 15mm of the target lesion for SABR.(23) For SABR treatments this will equate to a >10mm margin on the high dose region, i.e the planning target volume (PTV) which itself is a ≥5mm margin on the target lesion. Given there can be significant parenchymal atrophy and contraction around the SABR treated lesion with distortion of liver shape, a direct overlay of the PTV will not accurately depict the treated region over time. Similarly, it is acknowledged that a larger thermal ablation margin or in the case of SABR, the use of larger PTVs or development of larger volumes of off-target parenchymal contraction introduces some variability to this spatial definition.

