## Statistical Analysis Plan

A statistical analysis plan (SAP) will be finalised prior to datalock and contain additional detail on the methods described below.

All analyses will be performed according to an intention-to-treat protocol, with a per-protocol analysis performed as a sensitivity analysis. For the FFLP, PFS, TTP, ORR and OS endpoints, analysis will be performed comparing 2-year estimates from cumulative incidence (FFLP) and Kaplan-Meier survival curves (PFS and OS). The two comparisons between groups (SABR vs. MWA/RFA and SABR vs. SOC) will be analysed separately. Secondary analysis using Gray and log-rank tests will be performed to evaluate differences in overall time to event distributions. Fine and Gray, Cox proportional hazards regression will used to estimate hazard ratios with 95% confidence intervals. Secondary outcomes including the EORTC QLQ-C30 and QLQ-HCC18 (presented as mean scores over time) will be assessed using linear mixed-effects models to account for repeated measures. Additionally, time to deterioration (TTD) of combined GHS/QoL will be analysed. TTD will be defined as the time to first onset of a ≥10 point decrease from baseline. A 2-sided type-1 error rate of alpha=0.05 will be used for all hypothesis testing. All analysis will be performed using Stata software (version 17).

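### Section 8.2 defines stable disease with the text of complete response under both criteria, so two response categories overlap, truly stable lesions have none, and the ORR named in Section 14.6 has no sound basis

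*Protocol*

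**What the plan says.** Section 8.2 lists three non-progression categories, each with an mRECIST and a RECIST v1.1 line.

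- **CR and SD, mRECIST:** both entries read "mRECIST: The disappearance of any intratumoural arterial enhancement in the target lesion".
- **CR and SD, RECIST v1.1:** both entries read "RECIST v1.1: The disappearance of the target lesion (including all lymph node short axis diameters regressed to normal, i.e., short axis that shrinks to <1", the threshold being in centimetres.
- **PR, mRECIST:** "At least a 30% decrease in the longest viable tumour diameter of target lesion from baseline", with a matching 30% rule on lesion diameter for RECIST v1.1.

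Progression is defined separately. For typical lesions, Section 8.1.1 requires "an increase of ≥20% (compared to nadir) in longest diameter of viable arterial enhancing tumour with an absolute increase of ≥5mm".

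Section 8 makes these definitions operative: "The target lesion is to be assessed by mRECIST and RECIST v1.1 criteria" at each applicable follow-up timepoint until progression, with reference to 8.1, 8.2 and Figure 3.

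Section 1.6 says that mRECIST response predicts less well "in the early months following SABR, with the majority demonstrating stable disease".

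Section 14.6 states: "For the FFLP, PFS, TTP, ORR and OS endpoints, analysis will be performed comparing 2-year estimates". The sentence goes on to assign cumulative incidence to FFLP and Kaplan-Meier curves to PFS and OS. ORR is not defined anywhere in the protocol and appears in neither Table 2 (objectives and endpoints) nor Table 8 (endpoint definitions).

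**The concern.** A response classification has to be exhaustive and mutually exclusive. Section 8.2 is neither. It gives two labels to the best outcome and none to the middle one, under both criteria. Readers are told to apply it at every scheduled scan, 3-monthly to 2 years, so the error enters the data as they are collected. An analysis plan written later would not change the instruction that readers followed.

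The two faults also fall on different treatments. The overlap concerns lesions that lose enhancement. The missing category concerns lesions that keep enhancing without growing. Any comparison of response categories between arms could therefore be affected unequally, in a direction that depends on how sites resolved the ambiguity. ORR is the one named quantity that would be built on these categories, and Section 14.6 places it in a sentence about 2-year estimates from curves, which do not suit a response proportion.

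**Working it through.** The document gives no number that depends on the SD definition, so there is no stated figure to reproduce. The check is textual, followed by an illustration on assumed figures.

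**Step 1: compare the entries.** The CR and SD lines in Section 8.2 were compared as strings. They are identical for mRECIST and identical for RECIST v1.1.

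**Step 2: place lesions in the scheme as written.**

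| Lesion at follow-up | Category under 8.1 and 8.2 |
| --- | --- |
| No enhancement left (mRECIST), or lesion gone (RECIST v1.1) | CR and SD |
| Shrunk by 30% or more from baseline, not gone | PR |
| Grown by 20% or more and by 5 mm or more from nadir | PD |
| None of the above | none |

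**Step 3: compare with Section 1.6.** That section says a completely necrotic lesion may be scored as SD under RECIST v1.1. The lesion must then still be present, whereas 8.2 makes its disappearance the test for SD. Section 1.6 also describes persistent enhancement as common 3 to 12 months after radiation-based therapy and calls most early post-SABR lesions stable. Under 8.2, mRECIST SD would require that enhancement to have gone. Section 1.6 therefore uses the ordinary meaning of SD, and the 8.2 text looks like a copying error.

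**Step 4: see which arm each fault reaches.** The overlap reaches lesions that lose enhancement, mainly after ablation or TACE. On mRECIST, the missing category reaches lesions with persistent enhancement, mainly early SABR reads. Section 1.6 attributes the same pattern to radio-embolisation, so TARE patients in the Cohort 2 comparator share it.

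**Step 5: see what ORR does.** The mixes below are assumptions, not figures from the protocol.

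- Ablation-like: CR 80%, PR 5%, SD 10%, PD 5%.
- SABR-like, early: CR 20%, PR 20%, SD 55%, PD 5%.

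| Handling | Formula | Ablation-like | SABR-like |
| --- | --- | --- | --- |
| (a) CR + PR over all patients | CR + PR | 80 + 5 = 85% | 20 + 20 = 40% |
| (b) Overlap lesions coded SD | PR | 5% | 20% |
| (c) Uncategorised lesions dropped | (CR + PR) / (1 − SD) | 85/90 = 94% | 40/45 = 89% |

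The SD wording does not enter (a). Handling (b) distorts the ablation-like arm more (85% to 5%, against 40% to 20%). Handling (c) distorts the SABR-like arm more (40% to 89%, against 85% to 94%). With these mixes, the difference (ablation-like minus SABR-like) is 45 points under (a), −15 under (b) and about 6 under (c).

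**Step 6: check the other endpoints.** FFLP uses the progression rule in Section 8.1. PFS uses local progression or new lesions, and OS uses death. None refers to SD, and neither do the sample sizes in Section 14.1.

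**The case against.** The strongest reply is that this is a copying slip with little resting on it. CR, PR and PD are each usable as written, and ORR in its usual sense, CR plus PR over all patients, never touches SD. The protocol does not tell anyone to code complete responses as stable or to drop unclassified lesions. ORR is mentioned once and is not a listed endpoint, and the categories can be rebuilt if the diameters were recorded. Figure 3, to which Section 8 also sends readers, is not reproduced in the text available and may define SD correctly. The ORR mention in 14.6 could be a leftover label, since no curve is assigned to it and further detail is left to the analysis plan.

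Most of this stands, and it limits the consequences. It does not remove the error. Section 8.2 is cited by name as a rule for every read. If Figure 3 is correct, the two sources conflict and must be reconciled. The analysis plan can add detail on ORR, but the protocol sentence still lists an undefined response proportion among endpoints to be compared by 2-year estimates.

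A reader might go further and infer that ORR is wrong as written, or that the damage falls almost wholly on the SABR arm. The document supports neither. ORR goes wrong only under handling (b) or (c), and the CR/SD overlap falls mainly on the comparator side. Nor would the SD text lead early SABR lesions with persistent enhancement to be taken for complete responses, because they fail that text.

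**Conclusion.** The duplication is certain and Section 8.2 is wrong as written. Response categories recorded under it are unreliable in both arms, for different reasons. That no category exists for a stable lesion is established for Section 8.2 only, because Figure 3 cannot be checked.

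The effect on ORR is conditional, and its size cannot be derived from the document. The percentages in the illustration rest entirely on assumed response mixes. They show the direction of each fault and are not estimates. A reader might take them, or the remark in Section 1.6 that most early SABR lesions are stable, as evidence that ORR in the SABR arm will shift by tens of percentage points. The protocol gives no response distribution for either arm that would support this.

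The primary endpoint, PFS, OS and the sample sizes are unaffected. The correction should be made because the rule is applied at each scan and is cheap to repair, but it does not threaten the main result.

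**What to change.** - **Section 8.2:** replace both SD lines with neither sufficient decrease for PR nor sufficient increase for PD, using longest viable diameter for mRECIST and whole-lesion diameter for RECIST v1.1.
- **Figure 3:** check its SD definition and reconcile it with the corrected 8.2.
- **Data already entered:** re-derive response categories from the recorded diameters. This assumes that the diameters, and not only the category, were captured on the case report form.
- **Section 14.6:** take ORR out of the sentence on 2-year estimates. Either delete it, since it is in neither Table 2 nor Table 8, or report it descriptively as CR plus PR over all randomised patients at a fixed visit, naming the criterion used.

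The cost is two lines in 8.2, one edit in 14.6, a check of the case report form and a re-derivation of categories. No extra imaging, patients or follow-up are needed.

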## Management of Disease progression

See **Section 6.5 Treatment post progression**.

# PATIENT REPORTED OUTCOMES

Patient reported outcomes (PRO), an umbrella term referring to all outcomes and symptoms are directly reported by the participant. PROs have become a significant endpoint when evaluating the effectiveness of treatments in clinical trials. The following PROs will be administered:

## EORTC QLQ-C30

The EORTC QLQ-C30 consists of 30 items and measures cancer patients’ functioning and symptoms for all cancer types.(48) Questions can be grouped into 5 multi-item functional scales (physical, role, emotional, cognitive and social); 3 multi-item symptom scales (fatigue, pain, nausea and vomiting); a 2-item global health status scale; 5 single items assessing additional symptoms commonly reported by cancer patients (dyspnoea, loss of appetite, insomnia, constipation, diarrhoea) and 1 item on the financial impact of the disease.

## EORTC QLQ-HCC18

The EORTC QLQ-HCC is an 18 item instrument designed for use in parallel with the QLQ-C30 core instrument to assess all major dimensions of health-related quality of life in patients with HCC.(50, 51) The instrument is an 18-item scale, consisting of six symptom scales and two single items: fatigue (three items), body image (two items), jaundice (two items), nutrition (five items), pain (two items), fever (two items), sexual interest (one item), and abdominal swelling (one item). Scores are based on a 4-point Likert scale (with 1 = ‘not at all’ to 4 = ‘very much’); scaled scores for each domain ranged from 0–100 with a higher score indicating worse symptoms.

## Non-English speaking patients

This study may include participants that cannot read or write English. In this situation, one of the following options may be implemented in order to include these participants in the PRO component of the study:

1) The questionnaire will be supplied in the participants language

2) If the questionnaire is not available in the participants language, the assessment tool for that time point will not be given to the participant to complete.

The information regarding the collection of the PRO data will be documented on the Patient Reported Outcome (PRO) Completion and Missing Data (CoMiDa) checklist (Section 9.4 Patient Reported Outcome Completion and Missing Data).

## Patient Reported Outcome Completion and Missing Data

The Patient Reported Outcome (PRO) Completion and Missing Data (CoMiDa) checklist is a document developed by the Quality of Life office within the Psycho-oncology Co-operative Research Group (PoCoG)

The PRO CoMiDa checklist is a data management tool, designed to provide standardised documentation of the completion or reasons for non-completion of QOL assessments by participants in a clinical trial/study. Such documentation is crucial for quality assurance since missing data is the greatest threat to the integrity and interpretability of QOL data.

A PRO CoMiDa checklist has been included in the Case Report Form (CRF) suite for this trial. The person responsible for data collection at the site (i.e. Site Trial Coordinator, Data Manager, Research Nurse, or equivalent) must complete the PRO CoMiDa checklist at each scheduled time point.

## Completion of Patient Reported Outcome questionnaires

It is vital that the questionnaires completed within acceptable time limits surrounding the scheduled assessments (see **Table 5: Schedule of Assessments**). The completion rates of QoL forms will be monitored closely by the TCC. Specific instructions regarding the administration of PRO questionnaires are provided in the Data Management manual for this trial. These instructions must be followed to ensure the wellbeing of trial participants and the validity of PRO data. Please contact the TCC for further details.

# QUALITATIVE REVIEW OF THE PATIENT EXPERIENCE

A qualitative analysis of the participants’ perceptions of the treatments delivered during the trial is helpful to compliment the quantitative, efficacy outcomes of the trial. The primary aim of this qualitative review will be to investigate participants’ treatment experience with respect to overall treatment tolerability and satisfaction and how it varies according to the specific treatment received (SABR, percutaneous ablation, TACE). The data will assist with differentiating the participant treatment experience with different modalities, beyond other secondary outcomes such as adverse events.

An inductive, descriptive qualitative study design with qualitative interviews has been chosen.

## Number of participants

Sixty patients will be consecutively recruited over the duration of the study, with 15 patients from each of the four anticipated main treatments (SBRT, TACE, percutaneous ablation, combined TACE and percutaneous ablation).

## Recruitment and consent process

Participants will be invited to take part in the telephone interview by a delegated site staff member (e.g. their site study coordinator) within 4 weeks of treatment completion.

At this visit the delegated site staff member will;

- Inform the participant that;
  - the interview will take approximately 20 minutes
  - will involve briefly talking about their treatment experience in the trial
  - will be conducted by an interviewer from Flinders Medical Centre (South Australia), who is independent researcher from who is not part of the treatment or chief investigator research team
  - it is their choice to accept this invitation or not and if they consent, that they can change their mind and cancel the interview if they wish without effecting their continual care
- Obtain written consent from the participant for the designated interviewer to contact them for participation in the qualitative interviews and for site staff to pass on contact details to the interviewer.
- Site staff will pass on the name, study ID and contact details of the consented participant to the designated interviewer. These details WILL NOT be shared with the trial CRA or the chief investigator research team).

